### Intervention

The intervention will employ the approach applied in the Village Assani (Healthy Villages) by UNICEF’s nationwide sanitation program in the DRC in line with the guidelines of the government of the DRC and UNICEF on latrine improvement. The Korea Environment Corporation (KECO) and the Water and Sanitation for Africa (WSA), a Pan-African inter-governmental agency, will implement the project in collaboration with the Service Nationale Hydraulique Rural (SNHR: National Service for Rural Water Supply), DRC. The project is funded by the Korea International Cooperation Agency (KOICA).

### Project implementation

KECO will be responsible for supervision and management of the project implementation. Two sanitation experts have been deployed to this project team from the WSA to provide technical advice and three sanitation officials from SNHR have been seconded to facilitate community mobilization and provide information about the local culture, such as social norms and, if any, taboos during the project period.

Before the intervention, WASH committees were established right after 18 *quartiers* had been selected for the target area of the water supply program in February 2015; therefore, the committees were present in both the intervention and control arms. Nine WASH committee members were elected by the people living in each *quartier*. It was recommended that they elect at least three female members, but several *quartiers* could not recruit at least three female members to form their committee. The main roles and responsibilities of the WASH committee with regard to the water supply program are to maintain water facilities and collect water fees from the *quartier* residents. Later on, after 9 *quartiers* were selected for this sanitation intervention, we added new roles and responsibilities of the committee for latrine improvement for the intervention group and trained the committee members to perform those tasks. The new roles and responsibilities of the WASH committee are defined as (1) community mobilization on latrine improvement; (2) educating community people for healthier hygienic practices; (3) drawing and regularly updating the Sanitation Map; (4) monitoring the progress, especially on the ‘recording status of the Sanitation Calendar’ and ‘latrine improvement situation’ at the household-level in each *quartier*.

In order to promote increased coverage of well-equipped latrines, material subsidies, cement for making slabs, pit-hole covers and hand-washing facilities (cost US$7.50 per household), will be provided only to the households, regardless of their income level, who complete (1) pit digging and (2) construction of a superstructure and roof. Such conditions for the material support were determined in light of the availability and affordability of a superstructure, roof and pit-hole cover at the local level. The material subsidy is only partial and does not cover the whole cost of construction. The cost of a community member’s labor has been estimated at US$11.62 (10,750 Congolese Franc, exchange rate on July 7, 2015) per each household. According to the survey conducted in the trial, the average monthly income of one person was 21,500 Congolese Francs. The duration of latrine construction for each household is expected to be 10 full days when two people work together (including digging the pit, obtaining timber for the superstructure and thatches for the roof and its installation, molding the slab, making the cover, and installing the hand-washing facility) (Fig. 5).

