### Health outcomes assessment, sanitation calendar

The incidence of the diarrhea of the youngest child under four will be recorded by the mother or caregiver on the Sanitation Calendar distributed to each registered household in early August, 2015. The mother or caregiver will be educated to mark ‘O’ whenever her youngest child under four has diarrhea and mark ‘X’ on each day without diarrhea over the next 12-month period of longitudinal observation. Mothers were informed of the definition of diarrhea - three or more of watery stools in 24 h, with pictures of various stool types produced by the World Health Organization.

Households will be monitored by the WASH committee twice a month and instructed to keep recording appropriately. We employed the diary methodology to overcome the limitations reported in previous studies, such as recall bias [29] and reporting fatigue, leading to underestimation [30]. The diary methodology will allow us to capture more precisely the effects of well-equipped latrines on the duration of diarrhea and diarrheal incidence density. As an incentive for keeping a diary, the project has made the Sanitation Calendar a voucher, which can later be exchanged with a gift. During the monthly monitoring visit, the WASH committee will check the status of diary recording by taking a photo of the Sanitation Calendar marked as ‘O’ or ‘X’ for each day of each month.

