## Discussion

This trial aims to investigate the effects of well-equipped latrines when reaching up to a universal or sufficient level, rather than exploring the behavioral factors for latrine improvement. Recent studies [14, 15] with the same purpose failed to reach a universal or sufficiently high coverage level despite employing rigorous methodology; therefore the results can hardly indicate the true effects of high latrine coverage. For this reason, to come up with a solution to achieve the sufficiently high level of coverage, we paid close attention to the lessons learned from a study conducted in Bangladesh [31], whose results suggested that subsidies could increase latrine ownership both in subsidized and unsubsidized households. In the trial, material subsidies will be provided to all households in the intervention arm who complete the latrine improvement activities (e.g. digging a 1.5 m-deep pit, installing a superstructure and roof) in contrast to the selective subsidy provision in previous studies [14, 15]. It is critically important to mobilize community members to reach sufficient sanitation coverage. SNHR officials take on the responsibility to educate community members on the importance of improved latrines and encourage them to participate in the collective efforts to increase latrine coverage at the *quartier* level, and mobilize locally available materials and unskilled labor voluntarily to construct their household latrine.

The project will be effectively monitored through the ‘Sanitation Map’. The WASH committee will visit each household to monitor the latrine uptake progress and to draw the Sanitation Map for each *quartier* on a monthly basis (Fig. 6). The WASH committee drew a draft version of a Sanitation Map on a pilot basis in the run-up to the intervention (June 2015), and it was found that the WASH committee understood the objectives of sanitation mapping well enough for the project implementer to monitor progress. The Sanitation Map will be continuously updated through the early, middle and final stage of project implementation, both in the intervention and control arms.

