In addition, the Sanitation Calendar is to be used as an effective method of tracking diarrhea for a registered child. With the Sanitation Calendar, the incidence density of diarrhea can be calculated by dividing diarrhea cases by observed child numbers multiplied by the specific duration observed (e.g. week, month, etc.). This would be a more effective tool since it would cause less fatigue among the respondents, who would otherwise be asked to provide information about their children’s diarrheal episodes on a daily basis by interviewers. Assuming that the incidence of diarrhea among children is three times a year on average [32], the number of days marked ‘O’ in mothers’ diaries will not be very high. As for the duration of diarrhea, it was estimated at 10–20 days on average. Except for the days marked with ‘O,’ all the other days will be considered ‘X’. The Sanitation Calendar allows the day-to-day observation of diarrhea and resolves the limitations associated with the small number of clusters in the trial. Previous studies were unable to identify the effect of improved sanitation on diarrheal duration because they relied on the period prevalence of reported diarrhea. The utilization of the Calendar will enable us to explore a relationship between sanitation improvements and diarrhea and investigate the extent to which well-equipped and appropriately managed latrines affect disease duration. The measurement relying on caregivers’ reports, which are subjective in nature, is one of the limitations of this study. As we will not be able to conduct laboratory tests to assess children’s diarrhea incidence, there may be under-reporting or over-reporting of diarrhea. Despite this risk, we do not expect any significant difference of reporting patterns between the people of the intervention and control *quartiers*.

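### The protocol assigns Sanitation Calendar monitoring and its training to intervention-arm committees in one section and describes it without regard to arm in others, leaving a risk of differential ascertainment

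*Protocol article*

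**What the plan says.** **Project implementation.** WASH committees were formed in all 18 quartiers for the water program: "the committees were present in both the intervention and control arms". Their original main duties "are to maintain water facilities and collect water fees from the" quartier residents. Once nine quartiers had been picked to receive the latrine program, the section reports: "we added new roles and responsibilities of the committee for latrine improvement for the intervention group and trained the committee members to perform those tasks". Four new roles follow: (1) mobilization for latrine improvement, (2) hygiene education, (3) "drawing and regularly updating the Sanitation Map", and (4) "monitoring the progress, especially on the ‘recording status of the Sanitation Calendar" and on latrine progress in households.

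**Health outcomes assessment, sanitation calendar.** Each registered household receives a calendar in early August 2015. "Households will be monitored by the WASH committee twice a month and instructed to keep recording appropriately". The committee also photographs the calendar at a monthly visit. No arm is named.

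**Discussion.** The committee visits households monthly to draw the Sanitation Map, which is "continuously updated through the early, middle and final stage of project implementation, both in the intervention and control arms". Supervisory visits to the committee, calendar photographs and community review meetings are described without reference to arm. Any day not marked O is treated as X. On reporting, the protocol states that "we do not expect any significant difference of reporting patterns between the people of the intervention and control" quartiers.

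**The concern.** Incidence and duration are two of the three components of the primary outcome, and both depend on what mothers mark on the calendar. How completely they mark it depends partly on the committee that visits, reminds and checks. Read literally, Project implementation makes that outcome-measurement task part of the intervention package, and the only committee training it describes is training for that package.

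If the text were followed that way, trained committees would prompt mothers in one arm, while committees with no stated calendar duty or training would serve the other. The randomized contrast lies in the first phase, before control quartiers receive the intervention, so an imbalance then would fall directly on the main comparison. Because an unmarked day is read as diarrhea-free rather than missing, less prompting would lower the recorded rate and would not show up as missing data.

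**Working it through.** The protocol gives no figure to reproduce on this point. The check is a comparison of texts, followed by an illustration of size.

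**1. Who has the calendar task?**

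- Project implementation lists it as role (4), added for the intervention group, with training for the listed roles.
- The calendar section and the later Discussion text assign calendar visits and photographs to the WASH committee without an arm restriction. Calendars go to every registered household.
- No sentence expressly gives control committees the calendar task or training for it.

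**2. Is the role list really intervention-only?**

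- Role (3), the Sanitation Map, is in the same list. The Discussion has committees draw the map and keeps it updated in both arms.
- At least one listed role therefore operates in control quartiers, and the list cannot be taken as strictly intervention-only. Equally, the protocol never says which of the other roles extend to control.

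**3. What follows under each reading?**

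- If control committees do monitor calendars, Project implementation misstates who holds the role, and the protocol describes no training for them.
- If they do not, the arm-neutral descriptions are wrong and ascertainment differs by arm.
- Under both readings, passages describing the same outcome record conflict.

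**4. How large could the effect on incidence be?**

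Inputs from Sample size calculation: control rate 0.10 and intervention rate 0.075 per child-week, a true ratio of 0.075 / 0.10 = 0.75. Let r be the share of episodes captured in control divided by the share captured in intervention. The documents give no value for r; those below are assumptions.

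Observed ratio = true ratio / r.

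| r (assumed) | true ratio 0.75 | true ratio 1.00 |
|---|---|---|
| 1.00 | 0.75 | 1.00 |
| 0.95 | 0.79 | 1.05 |
| 0.90 | 0.83 | 1.11 |
| 0.85 | 0.88 | 1.18 |
| 0.80 | 0.94 | 1.25 |

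For example, at r = 0.90 the recorded control rate is 0.10 × 0.90 = 0.090, and 0.075 / 0.090 = 0.83. The planned 25% reduction appears as 17%. It would vanish only at r = 0.75 (0.75 / 0.75 = 1.00).

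The bias could also run the other way. The intervention committee promotes latrines, in a quartier rewarded for reaching 80% coverage. If that discouraged marking, r would exceed 1; at r = 1.10 the observed ratio is 0.75 / 1.10 = 0.68.

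For duration the direction is less clear. Unmarked days inside an episode shorten or split it, whereas missing whole short episodes lengthens the average.

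**The case against.** A reader might infer that control committees kept only their water duties and that control calendars were collected less intensively. The documents do not support that. The map is maintained in both arms. The calendar and Discussion sections, where outcome collection is actually specified, name no arm. Role (4) itself refers to each quartier. The phrase about the intervention group may simply be loose wording in a section about rolling out the project.

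Recording also has support beyond the committees. Mothers are taught to mark the calendar and are shown pictures to define diarrhea, the calendar can be exchanged for a gift, and supervisors check calendars directly in randomly sampled households. None of this is limited by arm. The protocol gives some grounds for expecting similar reporting: the hypothesis was not disclosed, and control quartiers receive the intervention later. Calendar photographs would allow recording to be compared between arms, and 7-day prevalence rests on recall rather than the calendar, so it offers a partial cross-check. It would be too strong to say that an imbalance could never be detected.

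These points stand, and they limit the finding to an inconsistency with a risk attached. They do not remove it. The undisclosed hypothesis and the phase-in bear on what mothers know, not on how often a trained committee prompts them. The other safeguards do not state that the committees' calendar task and training are equal in the two arms. Photographs can reveal unequal completeness but cannot recover unrecorded episodes.

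**Conclusion.** The concern holds as a contradiction about how a primary-outcome record is collected, with a real risk of differential ascertainment for incidence and duration. Project implementation ties calendar monitoring and its training to the intervention group; the calendar section and the Discussion do not. No text gives control committees the same task and training, so the expectation of equal reporting is not backed by a stated equal procedure.

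Actual unequal monitoring is not shown, and its size cannot be derived from the documents. The range of 0.79 to 0.94 for a true ratio of 0.75 rests wholly on assumed relative capture of 0.95 to 0.80 and on missed episodes being recorded as no diarrhea. In that direction a real benefit would be masked; the opposite direction cannot be excluded. Prevalence by 7-day recall is largely outside the problem.

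**What to change.** Reconcile Project implementation with the calendar section and the Discussion:

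- Take calendar monitoring out of the roles added for the intervention group, and state that the Sanitation Map role applies in both arms.
- Give all 18 committees the same calendar task, the same training before the August 2015 distribution, the same twice-monthly household visits and one photo schedule. At present, photographs are tied to a monthly visit in one place and to supervisory visits at least twice a month in another.
- Keep only mobilization and hygiene education, roles (1) and (2), specific to the intervention arm.
- Report visits made and calendar days completed by arm.
- Record blank days separately from days marked X.

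The article appeared in September 2017, after the planned calendar period. If collection has already taken place, the text should say what control committees were actually asked and trained to do, and by-arm completeness should accompany the incidence and duration results.

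The cost is a wording change and, if not already done, one training session for nine existing committees. The visits are those the calendar section already foresees. The downside is slightly more project contact in the control arm.

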**Fig. 5 Fig5:**
[figure not shown]
**a** A well-equipped latrine, **b** A well-equipped latrine, **c** A well-equipped latrine

### Health outcomes assessment, sanitation calendar

The incidence of the diarrhea of the youngest child under four will be recorded by the mother or caregiver on the Sanitation Calendar distributed to each registered household in early August, 2015. The mother or caregiver will be educated to mark ‘O’ whenever her youngest child under four has diarrhea and mark ‘X’ on each day without diarrhea over the next 12-month period of longitudinal observation. Mothers were informed of the definition of diarrhea - three or more of watery stools in 24 h, with pictures of various stool types produced by the World Health Organization.

Households will be monitored by the WASH committee twice a month and instructed to keep recording appropriately. We employed the diary methodology to overcome the limitations reported in previous studies, such as recall bias [29] and reporting fatigue, leading to underestimation [30]. The diary methodology will allow us to capture more precisely the effects of well-equipped latrines on the duration of diarrhea and diarrheal incidence density. As an incentive for keeping a diary, the project has made the Sanitation Calendar a voucher, which can later be exchanged with a gift. During the monthly monitoring visit, the WASH committee will check the status of diary recording by taking a photo of the Sanitation Calendar marked as ‘O’ or ‘X’ for each day of each month.

### Intermediate outcomes: exposure to excreta

#### Sanitary surveys

During the household survey period, data collectors will make an observation on the presence and quantity of feces within a certain distance of the household and *quartier.* The baseline survey conducted in January 2015 revealed that the majority of children under four practiced open defecation. Thus, latrine improvement activities will include the appropriate disposal of human feces, particularly of children and to encourage children to use well-equipped latrines.

### Vectors: fly counts

Previous studies have shown that fly control has a protective effect against diarrhea. We also examine the effect of well-equipped and appropriately managed latrines on fly control. To this end, glue traps will be used to count the number of flies. A sticky trap of the same length will be provided to data collectors so that they can place it around a pit-hole before administering the questionnaire during the household survey. After 30 min, they will check the traps and record the number of flies.

### Data analysis

Intention-to-treat analysis will be conducted to explore how well-equipped latrines reduce diarrhea incidence. To this end, the incidence density of diarrhea in children under four (diarrheal incidence per child-week, per child-month) and the reported diarrheal prevalence of the 7-day period will be calculated. Also, for other age groups (6–19, 20–39, 40 years and above), the reported diarrheal prevalence of the 7-day period will also be calculated. Generalized estimating equations will be used for the investigation at the cluster level. A log-binomial model will be used for calculating the incidence rate of diarrhea. The Random Effects model will be used, taking account of between-cluster variation based upon the assumption that there are cluster-level effects. Per-protocol analysis also will be conducted only as a contingency measure in cases where the coverage of latrines remains at an unexpectedly low level by the time when the intervention is completed. However, if we employ a per-protocol analysis, we cannot quantify the effects of well-equipped latrines, as this would break the comparability between the control and intervention groups obtained from randomization. Instead, we would note that per-protocol analysis is only an auxiliary analysis method to give additional background information. In addition, multi-level analysis will be conducted to investigate whether children living in the households without latrines could benefit from herd protection when a *quartier* reaches a certain level of latrine coverage (for instance, 70%).

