**Discussion:**

Material subsidies will be provided only to the households who complete pit digging plus superstructure and roof construction, regardless of their income level. This study employs a Sanitation Calendar so that the mother of each household can record the diarrheal episodes of her under-four child on a daily basis. The diary enables examination of the effect of the sanitation intervention on diarrhea duration and also resolves the limitation of the small number of clusters in the trial.

In addition, the project will be monitored through the ‘Sanitation Map’, on which all households in the study area, including both the control and intervention arms, are registered. To avoid information bias or courtesy bias, photos will be taken of the latrine during the household visit, and a supervisor will determine well-equipped latrine uptake based on the photos. This reduces the possibility of recall bias and under- or over-estimation of diarrhea, which was the main limitation of previous studies.

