### Sample size calculation

Based on the findings of the preliminary survey, we estimated diarrhea prevalence in Idiofa Territory to be 10%. We also made an assumption that the intervention would reduce the prevalence by 2.5% (25% relative reduction) on the basis of systematic reviews. Unlike the previous studies, we calculated sample size on the basis of *Incidence density of diarrhea by ‘child-weeks’* using formula [28] as follows:

The expected value of s^2^ is given by:

E(s^2^) = *λ* Av(1/y_j_) + *σ*
^2^
_c_ = *λ*Av(1/y_j_) + k^2^
*λ*
^2^,where λ is the true mean rate, y_j_ is the child-weeks of follow up in the j^th^ cluster, Av(1/y_j_) indicates the mean over all m clusters, σ^2^
_c_ is the between-cluster variance of true rates, and k is the coefficient of variation of those rates (22). Using the preliminary survey, we were able to determine that the overall diarrheal rate for the 20 *quartiers* was 0.1 (or 10 per 100 child-weeks). The empirical standard deviation of the observed diarrhea rates was s = 0.051216, and the average of the reciprocal child-weeks per *quartier* was Av(1/y_j_) =0.022222, so that k was estimated as follows:$$ {\widehat{\sigma}}^2=0.0{51216}^2\hbox{--} \mathrm{0.10.022222}=0.000401,\mathrm{therefore},\mathrm{k}=\surd \left(0.000401/0.1\right)=0.063 $$

With an assumption that the diarrhea rate in control *quartiers* remains constant at λ_0_ = 0.1, we required 80% power (z_β_ = 1.96) if the intervention is to reduce the diarrhea rate by 25% to λ_1_ = 0.10×0.75=.075. Assuming y = 540 child-weeks of observation in each *quartier*, the number of *quartiers* required in each treatment group is given by:$$ \mathrm{c}=1+{\left(1.96+0.84\right)}^2\left[\left(0.1+0.075\right)/540+{0.063313}^2\left({0.1}^2+{0.075}^2\right)\right]/{\left(0.1-0.075\right)}^2=6.14 $$

Ignoring clustering, y = (1.96 + 0.84)^2^(0.1 + 0.075)/(0.1–0.075)^2^ = 2195.2 child-weeks per group, corresponding to 2195.2/540 = 4.07 *quartiers*. Thus, the expected design effect for this trial would be 6.14/4.07 = 1.51.

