Assuming a coefficient of variation of 0.3 with 80% study power and 7.5% diarrheal prevalence in the intervention resulted in seven clusters (7 *quartiers*) per each arm. We increased the number of clusters to nine each in the control and intervention arm, and sampled 360 households in each trial arm. We will follow up at least 12 weeks to make 8640 child-weeks (‘child-weeks’ is the unit of the denominator) in each *quartier* as required to meet 80% power, considering a 12.5% loss to follow-up.

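### The Sanitation Calendar does not resolve the small number of clusters as the protocol twice claims, and the analysis of 9 v 9 quartiers states no small-sample method

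*Protocol article*

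**What the plan says.** Protocol article, Abstract (Discussion): the diary allows diarrhoea duration to be studied and "also resolves the limitation of the small number of clusters in the trial". The main Discussion, in the paragraph on the Sanitation Calendar, says that day-to-day observation "resolves the limitations associated with the small number of clusters in the trial".

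Sample size calculation: "We increased the number of clusters to nine each in the control and intervention arm, and sampled 360 households in each trial arm". That is 18 quartiers and about 40 households in each.

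Data analysis: "Generalized estimating equations will be used for the investigation at the cluster level". The same paragraph adds "A log-binomial model will be used for calculating the incidence rate of diarrhea" and "The Random Effects model will be used, taking account of between-cluster variation". It does not say which model gives the primary test, which standard error is used, what reference distribution applies, or whether there is a small-sample correction.

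Study design and Fig. 2: quartiers were placed in three strata by child diarrhoea prevalence, with two groups in each. Whole groups were allocated together so that a village stays in one arm. There were eight possible allocations.

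**The concern.** In a cluster trial the treatment comparison is limited by how much the clusters differ and by how many there are. Following each child for longer makes each quartier's rate more precise, but it does not make 18 quartiers into more than 18. The protocol recognises a small-cluster limitation and then declares it solved by something that cannot solve it.

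Two things are at stake. A reader may overrate what nine quartiers per arm can show. The analysis may also go ahead without a small-sample method because the problem is thought to be settled. The usual GEE sandwich standard error is too small on average with few clusters, so intervals would then tend to be too narrow.

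**Working it through.** **Inputs (Sample size calculation unless noted).** Rates 0.1 and 0.075 per child-week; y = 540 child-weeks per quartier in the formula; minimum follow-up 40 × 12 = 480; a 12-month diary (Health outcomes assessment) gives 40 × 52 = 2080; z values 1.96 and 0.84; 9 quartiers per arm; observed SD of quartier rates 0.051216; mean reciprocal child-weeks 0.022222; k printed as 0.063, and later as 0.3.

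**1. The plan's own figures.** "Ignoring clustering, y = (1.96 + 0.84)^2^(0.1 + 0.075)/(0.1–0.075)^2^ = 2195.2 child-weeks per group" reproduces: 7.84 × 0.175/0.000625 = 2195.2, and 2195.2/540 = 4.07. The printed 6.14 quartiers does not quite reproduce: 1 + 7.84 × [0.175/540 + 0.063313² × 0.015625]/0.000625 = 5.85. That is a separate matter and does not affect this point.

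**2. Which k.** The protocol defines k as the coefficient of variation of the quartier rates, with between-cluster variance k²λ². Its variance estimate is 0.051216² − 0.1 × 0.022222 = 0.000401, so k = √0.000401/0.1 = 0.20. The printed 0.063 is √(0.000401/0.1), which divides by the rate before taking the root. I therefore use 0.2 and the protocol's second value, 0.3.

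**3. What diary time can and cannot reduce.** The protocol's variance is λ·Av(1/y) + k²λ². Child-weeks appear only in the first term. Quartiers needed per arm by the protocol's formula:

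| k | y = 480 | y = 2080 | unlimited y |
|---|---|---|---|
| 0.2 | 13.4 | 9.9 | 8.84 |
| 0.3 | 23.2 | 19.7 | 18.64 |

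The last column is 1 + 7.84 × k² × 0.015625/0.000625 = 1 + 196k². Rounded up, that is 9 and 19.

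Power with 9 per arm (z-test, with t on 16 df in brackets):

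| k | y = 480 | y = 2080 | unlimited y |
|---|---|---|---|
| 0.2 | 66% (61%) | 80% (75%) | 85% (80%) |
| 0.3 | 43% (39%) | 49% (45%) | 52% (47%) |

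**4. Type I error if the GEE were uncorrected.** Simulation under no effect: 9 v 9 quartiers, equal child-weeks, Poisson counts, gamma or log-normal quartier rates, log link, sandwich standard error, cut-off 1.96, k = 0.2 and 0.3.

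- *Independent quartiers, no stratum effect:* about 8.4–8.9%. An analytic approximation, 2·P(t₁₆ > 1.96√(8/9)), gives 8.3%. A child-level exchangeable GEE gives 8.1% (Monte Carlo SE 0.9).
- *Diary length:* at k = 0.2 in one set of runs, 8.5% with 480 child-weeks per quartier and 8.4% with 2080. More diary time does not repair it.
- *Correction:* Kauermann-Carroll standard errors with t on 16 df give about 5%.
- *Unequal exposure (assumed CV 0.4 to 0.65):* roughly 9–11% uncorrected.
- *Strata explain 25–50% of between-quartier variance (assumed), strata ignored in the analysis:* about 5–7%.
- *25–50% of that variance shared within jointly randomised groups (assumed; group sizes 5, 5, 2, 2, 2, 2, where only the two fives are given in the text):* about 15% (25% shared, k = 0.2, 480 child-weeks) to 29% (50% shared, k = 0.3, 2080 child-weeks). With the 16-df correction, about 10–22% remains.

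**5. Randomisation test.** With eight equally likely allocations the smallest two-sided p-value is 2/8 = 0.25, so this route cannot give significance at 5%.

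**The case against.** Four points on the other side carry weight.

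- *The article does not specify an uncorrected GEE.* It names the method and is silent on the standard error and reference distribution, which an analysis plan that is not shown may settle. It also names a random effects model and does not say which model is primary. A reader might infer that the plan's main test has an 8–9% error rate. The documents do not support that; the figure is what one possible implementation would give.
- *The article never offers the diary as a reason to omit a correction.* A reader might draw that link, but the two passages on the diary do not mention standard errors or tests.
- *The diary does help.* At k = 0.2, going from 12 weeks to 12 months raises z-test power from 66% to 80%. With the printed k of 0.063, unlimited diary time would need only 1.8 quartiers per arm, and the limitation would look nearly gone. That value, however, is not the coefficient of variation that the protocol defines.
- *Stratification works against the inflation.* Balanced strata that are left out of the model make the standard error conservative, and this can offset the sandwich bias entirely.

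All four narrow the point about GEE. None of them makes the diary statement true, because it is an assertion about the design and not a detail left for later.

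**Conclusion.** The statement that the calendar resolves the small number of clusters is wrong, and the protocol's own variance formula shows it. This conclusion does not depend on any analysis choice. At k = 0.3 no amount of diary time makes nine quartiers per arm enough (19 needed). At k = 0.2 nine per arm suffices only in the limit of unlimited diary time. In both cases the number of quartiers, and hence the degrees of freedom, is unchanged.

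The type I error is a conditional risk. For an uncorrected sandwich with a normal reference it is about 8–9% under independence, equal quartier sizes and no stratum effect. It runs from about 5% to 29% over the assumed shares for strata and joint allocation. The protocol gives no data on those shares, so neither end can be ruled out. The concern is worth acting on because the correction is cheap and the text now suggests that the matter is closed.

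**What to change.** 1. In the Abstract and the Discussion, delete the claim or reword it to say that the diary improves precision within quartiers only, and that the number of quartiers remains a limitation.
2. State which analysis is primary and give it a small-sample method. One option is a quartier-level analysis of log rates adjusted for the three randomisation strata with a t reference (18 − 4 = 14 df, critical value 2.14 instead of 1.96). The other is GEE with a Kauermann-Carroll or Fay-Graubard correction and t degrees of freedom.
3. Add a sensitivity analysis that takes the six jointly allocated groups as the unit, because a correction that assumes 18 independent quartiers does not hold 5% if groups share variance.

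The cost is a few sentences and standard software options, plus wider intervals and some power: about 4 to 5 percentage points for t on 16 df against z in the power table. The loss is severe only in the group-level analysis. Six units leave 4 df, or 2 df after adjusting for strata, with critical values of 2.78 and 4.30. It should be presented as a check on robustness and not as the main test.
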